#### 10.2.1.4 PROCEDURE IN THE INTERVENTION GROUP DURING AND AFTER BIRTH

In the intervention group, the infant is delivered by obstetrics together with the placenta. Here, birth occurs either in the intact amniotic sac or, when the amniotic sac is open, by gently detaching the placenta from the uterus. In any case, the infant is transferred with the umbilical cord and placenta still intact by the obstetrician or midwife to the neonatal resuscitation unit of the neonatology department.

If the amniotic sac is still intact, the neonatologist opens it on the neonatal resuscitation unit.

Neonatal resuscitation is also provided according to the internal clinical standards: the infant is covered with an occlusive polyethylene wrap (NeoWrap™, Fisher&Paykel Healthcare Limited, Auckland, New Zealand) for temperature management, the infant is placed in the left lateral position (so-called "comfort position") and the neonatologist initiates respiratory support using a CPAP mask according to a standardized internal protocol. At the same time, the nurse establishes standardized monitoring, which includes transcutaneously measured blood oxygen saturation, heart rate, respiratory rate and respiratory volumes. An NIRS monitoring is also established, analogous to the procedure in the control group.

Additionally, a further staff member (neonatologist 2 or nurse 2 or midwife) stores the placenta in a sterile plastic bag (neoHelp, Vygon, Aachen, Germany) immediately after opening the amniotic sac or after transferring the infant to the neonatal resuscitation unit, where it remains until umbilical cord is clamped. The placenta is sterilely stored and weighed on a separate kitchen scale, then kept at a level of about 40 cm above the infant's umbilicus for EPT. The exact level depends on the length of the

infant's umbilical cord and can therefore vary individually. EPT is to be performed from the time the placenta is held up for a period of at least 1 minute but not more than 10 minutes. After umbilical cord clamping, placenta shall be weighed again on the separately provided calibrated kitchen scale and the weight documented.

The arrangement in the neonatal resuscitation of the intervention group is shown in Figure 2.

[figure not shown]

Figure 2: Arrangement in neonatal resuscitation of infants in the intervention group.

#### 10.2.1.5 PROCEDURE FOR TWINS DURING AND AFTER BIRTH

The intervention according to the randomization is only to be performed on **twin 2** (Section 9.7). **Twin 2** is then transferred to the neonatal resuscitation unit where the extended respiratory function monitoring device (with measurement of tidal volume, PEEP, mean airway pressure, cerebral oxygenation) is located. For space limitations, this is usually the left neonatal resuscitation unit in the delivery room of the University Hospital of Cologne.

The firstborn infant (twin 1) is transferred to the right resuscitation unit without extended respiratory function monitoring after birth and DCC or the procedures described in Section 10.2.1.3. The neonatal resuscitation is otherwise analogous to the procedures explained in Section 10.2.1.3.

#### 10.2.1.6 PROCEDURE IF INTERVENTION IS NOT PERFORMED

If, despite allocation of the infant to the intervention group, the development of the placenta by obstetrics is not possible (e.g. deep placental position) or if there are concerns by the obstetrics (long duration of development, maternal complications such as severe blood loss, etc.), it is up to obstetrics to stop the intervention in this situation and, if necessary, to immediately clamp the cord (ICC) or perform umbilical cord milking (CM). In this case, the further procedure of neonatal resuscitation is

based on the procedure of the control group. Nevertheless, the collection of primary and secondary target criteria is performed. (intention-to-treat principle).

## 10.2.2 SECOND STUDY PERIOD

During the hospital admission, baseline patient data and target neonatal and maternal outcome data are collected as part of the patients' standard medical record.

### 10.2.2.1 MANAGEMENT WITH THE USE OF RED BLOOD CELL CONCENTRATES

During the infants' admission to the hospital in the second study period, the indication for transfusion of RBCT concentrates is based on the "liberal RBCT thresholds" defined in the "Effects of Transfusion Thresholds on Neurocognitive Outcome of Extremely Low Birth-Weight Infants" (ETTNO)-trial (34):

| Time after randomization | Hematocrit, %               |             |                         |             |
|--------------------------|-----------------------------|-------------|-------------------------|-------------|
|                          | restrictive RBCT thresholds |             | liberal RBCT thresholds |             |
|                          | critical                    | noncritical | critical                | noncritical |
| 3–7 days of age          | <34                         | <28         | <41                     | <35         |
| 8–21 days of age         | <30                         | <24         | <37                     | <31         |
| >21 days of age          | <27                         | <21         | <34                     | <28         |

'Critical' refers to state of health and is defined as the presence of any of the following: (1) requirement of mechanical ventilation (any mode, excluding continuous positive airway pressure), (2) requirement of continuous positive airway pressure with  $\text{FiO}_2 > 0.25$  for >12 h per 24 h, (3) patent ductus arteriosus requiring therapy, (4) more than 6 apneas that require stimulation per 24 h, or more than 4 desaturations to  $\text{SpO}_2 < 60\%$  per 24 h despite methylxanthines and continuous positive airway pressure and (5) acute sepsis or acute necrotizing enterocolitis requiring inotropic or vasopressor support.

Figure 3: Thresholds for infusion of red cell concentrates in the ETTNO study. From: (34)

Figure 3 illustrates the hematocrit thresholds for RBC transfusion. To meet the definition of critical condition, at least one of the following points must be fulfilled:

- Ventilation including non-invasive positive pressure ventilation (DuoPAP ventilation, high frequency oscillation) and invasive ventilation.
- Non-invasive respiratory support with CPAP and  $\text{FiO}_2$  requirement > 0.25 for more than 12 hours within the last 24 hours
- Concurrent therapy (medical or surgical) to close a persistent ductus arteriosus
- More than 6 apneas requiring stimulation within the past 24 hours or more than 4 desaturations with an  $\text{SpO}_2 < 60\%$  in 24 hours despite administration of methylxanthines and CPAP therapy
- Acute Sepsis or NEC requiring inotropic or vasopressor support.

#### **10.2.2.2 DIAGNOSIS OF IVH**

Cerebral ultrasound examinations are performed independently of the study by the physicians of the Department of Pediatric Radiology of the Institute of Diagnostic and Interventional Radiology, University Hospital Cologne. The examining physician is blinded to the intervention in the delivery room, i.e. does not know which intervention (EPT or DCC) was performed on the infant. The radiological diagnosis is based on the criteria of Papile et al (16).

#### **10.2.2.3 EXPERIMENTAL PART**

For the experimental part of the study, analyses of patient blood samples from both study arms will be performed at two time points. For this purpose, blood from the patient's umbilical cord will be collected (0.5 ml) after the patient's cord has been cut, and 0.5 ml of blood will be collected on the patient's 28th day of life ( $\pm 2$  days) as part of a routine blood sampling. After sample collection, this blood is identified with a prepared label giving the patient's randomization ID. The serum will be centrifuged immediately afterwards in the perinatal center and will be stored at  $-20^{\circ}\text{C}$ . Further examinations are performed in the Laboratory of Experimental Pneumology of the Department of Pediatrics and Adolescent Medicine or in the Center for Molecular Medicine Cologne (ZMMK). No additional data will be collected or separate blood samples taken as part of the study.

The serum samples of the patients are delivered to the ZMMK (Laboratory: Comparative Medicine, Head: PD [name]) following the strict cold storage. A quantitative determination of pro-/anti-inflammatory and angiogenic factors is performed by enzyme-linked immunosorbent assay (ELISA). The Bio-Plex multiplex system (Bio-Plex 200®, Bio-Rad Laboratories, Inc., Hercules, CA, USA) is used for this purpose. The frozen samples are defrosted at room temperature and processed in the multiplex system according to the manufacturer's instructions. After measurement, analysis of the raw data is performed using Bio-Plex Manager™ software (Bio-Rad). Based on the median fluorescence intensity, the concentration of cytokines for each sample is calculated by the system and given in pg/ml.

If abnormalities are found here, the use of residual serum material collected from the patients is planned. This second step of the analysis provides for an exposure of commercially available human pulmonary microvascular endothelial cells (HPMVEC) (ScienceCell, [name]) to the patient serum in order to investigate possible influences on the homeostasis of the endothelial cells. The performance of these experiments is dependent on the amount of residual material. This will be done by standardized molecular genetic methods and will primarily involve measurement of cell proliferation by MTT assay (Promega) for which a small amount of residual material is required and/or BrdU assay (Roche) and secondarily "tube formation assay" as well as cell migration.

#### **10.2.3 THIRD STUDY PERIOD**

At the corrected age of the child of  $24 \pm 2$  months, neurocognitive development is assessed by using the Bayley's psychomotor developmental index (PDI) and the mental developmental index (MDI) based on the Bayley Scales of Infant Development (BSID III). This examination takes place as part of

the legal outpatient follow-up of VLBW children at the Social Pediatric Center (SPC) of the Department of Pediatrics and Adolescent Medicine and is recorded as part of the medical follow-up.

For this follow-up of infants, it is ensured that the investigator is blinded to the allocation of the infant to intervention or control group in order to avoid bias.

## **11 OVERALL DURATION OF THE TRIAL**

The recruitment period is approximately 12 months (end of first study period), the discharge of the last recruited patient is about 16 months after the start of the study (end of second study period), the trial is completed after developmental neurological examination of the last recruited patient after about 3.5 years.

## **12 BENEFIT RISK CONSIDERATION**

### **12.1 INDIVIDUAL BENEFITS ASSOCIATED WITH STUDY PARTICIPATION**

The aim of the trial is to investigate the influence of EPT on postnatal blood volume and neonatal outcome of preterm infants with a birth weight lower than 1500 grams. If the hypothesis is confirmed, EPT will lead to a higher postnatal blood volume, resulting in a hemodynamic stabilization of the infants in the first days of life. In the positive case, this may result in a reduction of anemia with the need for donor blood transfusions, as well as a lower incidence of, for example, IVH, BPD as typical neonatal complications, and better long-term neurological development. EPT might thus contribute to a better long-term outcome of very small preterm infants.

### **12.2 RISKS AND EXPOSURES ASSOCIATED WITH STUDY PARTICIPATION**

On the other hand, no relevant risks are known from clinical experience and previous retrospective studies. Theoretically, however, it is possible that EPT may cause polyglobulia resulting in hyperviscosity due to the transfusion of umbilical cord blood. Because of the increased accumulation of hemoglobin, there could be subsequent aggravation of neonatal hyperbilirubinemia. However, there was no evidence for this in the retrospective data analysis from 2015 (8).

Since the collection of the additional blood samples required as part of the study is performed only as part of necessary routine blood sampling, additional stress, pain, and irritation to the infant are minimized.

The sample volume required from the blood collection on day 28 of life is 500µl (0.5ml). According to EMEA recommendations, a single study-related blood sample in premature and newborn infants should not exceed 1% of the infant blood volume, and in the case of multiple blood samples, should not exceed 3% of the infant blood volume cumulatively (22). Based on an infant blood volume of 80 (-100) ml/kg, the first benchmark of 1% would be met by drawing 500µl of blood from an infant body weight of at least 625g ( $0.625\text{kg} \times 80\text{ml} = 50\text{ml}$  blood volume.  $0.5\text{ml} / 50\text{ml} = 1\%$ ). The smallest patients included in the study will be the equivalent of 28 weeks' gestation at the time of blood collection. At this time, the mean body weight is approximately 1000g (23). The collection of 500µl of blood therefore amounts to approximately 0.6% of the infant blood volume, thus no relevant impact of the blood collection on the infants can be assumed.

Overall, we therefore conclude that the risk-benefit ratio is positive.

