## **9 STUDY POPULATION**

### **9.1 INCLUSION CRITERIA**

- Birth weight < 1500 gram ("very low birth weight infant")
- Gestational age at birth >23+6 weeks
- Delivery by cesarean section
- Delivery in the tertiary care perinatal center of the University Hospital Cologne
- Written consent of the legal guardian

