## **10 STUDY PROCEDURE**

### **10.1 SCREENING AND ELIGIBILITY ASSESSMENT**

The informed consent of the parents or legal guardians is obtained prior to birth at the Department of Gynecology and Obstetrics, according to the inclusion and exclusion criteria. Reasons for an expected premature birth are maternal (e.g. pre-eclampsia, HELLP syndrome, cervical insufficiency, amniotic infection) or fetal (e.g. intrauterine growth retardation, pathological CTG) pregnancy complications. For this purpose, pregnant women > 23+6 weeks' gestation and < 32 + 0 post menstruationem, in whom premature delivery of the infant is expected < 32 + 0 gestational age and in whom the estimated birth weight of the infant is < 1500 grams, will be informed about the study as potential study participants.

The infant will only be included in the study if the legal guardians (usually both parents, in the case of a single parent, the sole legal guardian) have given their consent after they have been informed about the nature, significance and scope of the trial in an appropriate and comprehensible way, by a physician of obstetrics and neonatology, both orally and in writing, and at the same time have declared with their consent that they agree with the recording of data that will take place within the framework of the trial. If there is a twin pregnancy, a signed declaration of consent from the legal guardians must be available for each infant.

The parents are informed that they can withdraw their consent at any time without giving reasons and without any disadvantages for their infant or themselves. The original written consent will be kept in the study folder at the study center. A copy of the written information and informed consent will be given to parents and guardians.

Since a large number of the described complications leading to premature birth can occur in acute and also unexpected ways, prenatal informed consent of both guardians is not always possible (e.g. in case of a business trip of the father). In this case, the second guardian (usually the father) is informed as soon as possible after birth. If consent is then refused, the infant will be excluded from the study.

The original of the information for the legal guardians and the written consent form will be kept in a study folder in the study center.

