### 14.5 EXPERIMENTAL PART

- Serum analysis by multiplex angiogenesis panel, taken from the umbilical cord after cord clamping:
  - **Pro- and anti-inflammatory cytokines:** IL-1 $\alpha$ , IL-1 $\beta$ , IL-6, IL-10, IL-12 (p40), IL-12 (p70), IL-13, IL-17A, granulocyte colony-stimulating factor (G-CSF), granulocyte/macrophage colony-stimulating factor (GM-CSF), monocyte chemotactic protein-1 (MCP-1), macrophage inflammatory protein-1 $\alpha$  (MIP-1 $\alpha$ ), MIP-1 $\beta$ , CXCL10,
  - **Factors of Angiogenesis:** sALK-1, amphiregulin, TGF $\alpha$ , epidermal growth factor (EGF), angiopoietin-1/2, sCD31/PECAM-1, endoglin, endothelin-1, basic fibroblast factor (FGF2), hepatocyte growth factor (HGF), leptin, placental growth factor-2 (PLGF-2), prolactin, vascular endothelial growth factor-A (VEGF-A), VEGF-C and VEGF-D, Placental growth factor (PGF), BMP2, BMP4, BMP7, TGF $\beta$ , apelin
- Serum analysis of 0.5 ml blood sample collected on day 28 of life ( $\pm 2$  days) as part of a medically indicated blood collection. Analysis by multiplex angiogenesis panel on:
  - **Pro- and anti-inflammatory cytokines:** IL-1 $\alpha$ , IL-1 $\beta$ , IL-6, IL-10, IL-12 (p40), IL-12 (p70), IL-13, IL-17A, granulocyte colony-stimulating factor (G-CSF), granulocyte/macrophage colony-stimulating factor (GM-CSF), monocyte chemotactic protein-1 (MCP-1), macrophage inflammatory protein-1 $\alpha$  (MIP-1 $\alpha$ ), MIP-1 $\beta$ , CXCL10,

- **Factors of Angiogenesis:** sALK-1, amphiregulin, TGF $\alpha$ , epidermal growth factor (EGF), angiopoietin-1/2, sCD31/PECAM-1, endoglin, endothelin-1, basic fibroblast factor (FGF2), hepatocyte growth factor (HGF), leptin, placental growth factor-2 (PLGF-2), prolactin, vascular endothelial growth factor-A (VEGF-A), VEGF-C and VEGF-D, Placental growth factor (PGF), BMP2, BMP4, BMP7, TGF $\beta$ , apelin

Differences and changes in the panel variables are described with fold change (to base 2) and evaluated with distribution-free procedures (Wilcoxon rank sum or Wilcoxon signed rank test). The false discovery rate is controlled at 5% (Benjamini Y, Hochberg Y: Controlling the false discovery rate: a practical and powerful approach to multiple testing. Journal of the Royal Statistic Society 1995; 57: 298-300).

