## **16 BIOMATERIALS MANAGEMENT**

In the study, blood is collected at two time points. The first collection of approximately 0.5 ml of whole blood is taken from the umbilical vein of the umbilical cord, after the placenta has been detached from the infant's blood circulation, and thus does not represent a direct intervention on the patient. The second blood sample is taken on the 28th day of life ( $\pm 2$  days) as part of a medically indicated blood sampling. The blood volume is 0.5 ml of whole blood.

Immediately after the blood sampling, the serum is centrifuged by a centrifuge located in the perinatal center, which is used in daily clinical routines for the centrifugation of blood samples. The samples are labeled with prepared stickers using the randomization ID. On the one hand, this makes the blood samples anonymous, on the other hand, it is still possible for the study management to assign the samples to the individual patients. After centrifugation, the serum is immediately stored at  $-20^{\circ}\text{C}$  in the freezer of the perinatal center until final use.

Beyond that, no further blood sample collection beyond routine testing will occur.

Placenta and umbilical cord will be transferred to the obstetrics department for further use or disposal as usual after completion of EPT in the intervention group.

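### The 0.5 ml day-28 research sample is justified by a mean weight of about 1000 g, which does not show that the lightest eligible infants stay within the protocol's own 1% limit

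*Protocol*

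**What the plan says.** Section 12.2 takes from a regulatory guideline the recommendation that a single study-related sample "should not exceed 1% of the infant blood volume", with 3% as the cumulative figure. "Based on an infant blood volume of 80 (-100) ml/kg", it calculates that 0.5 ml meets the 1% figure from a body weight of 625 g.

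It then turns to the participants: "The smallest patients included in the study will be the equivalent of 28 weeks' gestation at the time of blood collection". The next sentence supplies a weight: "At this time, the mean body weight is approximately 1000g". From this it derives a draw of about 0.6% of blood volume, states that no relevant impact is to be expected, and goes on to call the overall risk-benefit ratio positive.

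Elsewhere in the protocol:

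- Section 9.1 admits infants below 1500 g from 24+0 weeks and gives no lower weight limit. Section 9.2 lists no exclusion for low weight or growth restriction.
- Section 10.1 includes, among the reasons for the expected preterm birth, "fetal (e.g. intrauterine growth retardation, pathological CTG) pregnancy complications".
- Section 14.5 plans "Serum analysis of 0.5 ml blood sample collected on day 28 of life", and section 16 says "The blood volume is 0.5 ml of whole blood". Section 10.2.2.3 gives the same volume. None of the three makes it depend on the infant's weight.

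**The concern.** The limit applies to each infant, but the argument for meeting it rests on an average. Section 12.2 treats the youngest participants as the smallest and then gives the smallest the mean weight for their age. Neither step is sound: an infant can be light for its gestational age, and by definition some infants lie below the mean. The protocol also expects to recruit from pregnancies complicated by growth restriction, where low weight for age is the point.

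The 625 g threshold is calculated but has no operational role. No eligibility criterion keeps lighter infants out, and no sampling instruction responds to a weight below it. What is at stake is the accuracy of a safety statement on which the risk-benefit conclusion partly relies, and it concerns the most vulnerable part of the eligible population.

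**Working it through.** **Inputs from the protocol.** Sample volume 0.5 ml (10.2.2.3, 14.5, 16). Single-sample limit 1% of blood volume, blood volume 80 ml/kg with 100 ml/kg as the upper value, and mean weight about 1000 g (all 12.2).

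**1. The protocol's own figures.** Threshold weight = volume / (0.01 × blood volume per kg).

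- At 80 ml/kg: 0.5 / (0.01 × 80) = 0.625 kg = 625 g, as stated.
- At 100 ml/kg: 0.5 / (0.01 × 100) = 0.500 kg = 500 g.

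Share drawn = volume / (blood volume per kg × weight). At 1000 g and 80 ml/kg: 0.5 / 80 = 0.625%, reported as about 0.6%. The arithmetic in 12.2 is correct. The age also follows: 24+0 weeks plus 28 days is 28+0 weeks.

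**2. Share drawn at lower day-28 weights.**

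| Weight on day 28 | at 80 ml/kg | at 100 ml/kg |
|---|---|---|
| 625 g | 1.00% | 0.80% |
| 600 g | 1.04% | 0.83% |
| 550 g | 1.14% | 0.91% |
| 500 g | 1.25% | 1.00% |
| 450 g | 1.39% | 1.11% |
| 400 g | 1.56% | 1.25% |

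**3. Which birth weights this could concern.** The protocol gives no growth data, so this step is an assumption: birth weight is regained at day 10, followed by 18 days of growth at 10 to 20 g/kg/day. The growth factor is 1.01^18 = 1.196 to 1.02^18 = 1.428.

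- At 80 ml/kg: 625 / 1.428 = 438 g to 625 / 1.196 = 523 g.
- At 100 ml/kg: 500 / 1.428 = 350 g to 500 / 1.196 = 418 g.

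As a sensitivity check, a constant net gain of 0, 5, 10 or 15 g/kg/day over all 28 days puts the cut-off at 80 ml/kg at 625, 544, 473 or 412 g.

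**4. Size of an excess.** An infant of 400 g at birth, at the slower rate, weighs 400 × 1.196 = 478 g on day 28. At 80 ml/kg, 1% of its blood volume is 0.01 × 80 × 0.478 = 0.38 ml, so 0.5 ml is about 0.12 ml over, or 1.31%. At 500 g birth weight the day-28 weight is 598 g, the 1% volume is 0.48 ml and the excess about 0.02 ml.

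**5. How many infants.** This cannot be derived, because the protocol gives no weight distribution. Purely as an illustration, suppose weights at 28 weeks were normal with mean 1000 g. The share below 625 g is Φ((625 − 1000)/SD): about 0.01%, 0.6%, 3% and 7% for SDs of 100, 150, 200 and 250 g. This describes only the youngest participants, and the trial has 60 births.

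**The case against.** The case for leaving section 12.2 alone has several parts.

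- **The text is more careful than it looks.** It cites a recommendation, calls 1% a benchmark and states the 625 g threshold openly. It nowhere says outright that every infant complies. That is fair, but the paragraph presents the mean as covering the smallest patients and draws its reassurance from that.
- **Few infants, if any, will be affected.** An infant must be very light at birth, survive to day 28 and have a medically indicated draw at that time. The exclusion for fetal or maternal compromise in section 9.2 may also remove some severely growth-restricted fetuses. This stands. It limits the size of the point but does not supply the missing weight condition.
- **The excess is small.** At 100 ml/kg the threshold falls to 500 g, and at 80 ml/kg the excesses worked out above are about 0.02 to 0.12 ml. The 3% cumulative figure is not in play: one 0.5 ml draw would reach it only at 0.5 / (0.03 × 80) = 0.208 kg, and under section 16 the cord sample is taken once the placenta is separated from the infant's circulation. This stands too, but the 1% figure still applies to the single sample.
- **The blood is drawn with routine sampling.** Section 12.2 offers that as a way to limit pain and stress. It still applies the 1% figure to the 0.5 ml.

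A reader might go further and infer that the trial will in fact take more than its limit from its smallest infants. The documents do not support this, because it presumes that such infants are enrolled and sampled. A reader might also argue that the 1000 g figure does not suit an infant born four weeks earlier. That depends on a cited growth reference whose content is not in the protocol, and the point does not need it.

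**Conclusion.** The point holds as a gap between the safety argument and the design. On the protocol's own inputs, an eligible infant weighing less than 625 g on day 28 would exceed the 1% limit at 80 ml/kg, and one below 500 g would exceed it even at 100 ml/kg. Nothing in eligibility or the sampling instructions prevents this. The calculations in section 12.2 are right; the step from a mean weight to the smallest patients is not.

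The practical size is modest. The birth-weight ranges (438 to 523 g at 80 ml/kg, 350 to 418 g at 100 ml/kg) rest on assumed growth. The number of infants is unknown, probably small and possibly zero, and no harm is shown. The primary outcome, randomisation and sample size are unaffected; only the justification of one exploratory sample is.

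**What to change.** Reconcile section 12.2 with sections 9.1, 10.1, 10.2.2.3, 14.5 and 16, so that the day-28 research sample is tied to the infant's current weight through the 1% limit and the 625 g calculation that the protocol already contains. In 12.2, replace the mean-weight argument and the blanket figure of about 0.6% with a statement that is true of each infant sampled. How this is put into practice is for the sponsor to decide.

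The cost is a short amendment to the sampling sections and the risk paragraph. A few day-28 serum samples in the exploratory part may be smaller or missing.
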